# Impact of a “vegetables first” approach to complementary feeding on later intake and liking of vegetables in infants: a study protocol for a randomised controlled trial

**DOI:** 10.1186/s13063-021-05374-7

**Published:** 2021-07-26

**Keywords:** Infants, Weaning, Introducing vegetables, Food preference, Vegetable intake

## Abstract

**Background:**

Vegetables as first complementary foods for infants may programme taste preferences that lead to improved vegetable intake in children. Yet few studies have investigated the impact of a ”vegetables first” approach to complementary feeding, especially in New Zealand. The purpose of this randomised control trial is to investigate the effect of starting complementary feeding with vegetables only on infants’ later intake and liking of vegetables, compared to those starting with fruit and vegetables.

**Methods/design:**

One-hundred and twenty mother-infant pairs living in Auckland, New Zealand, will be randomised to receive either vegetables only (intervention) or fruit and vegetables (control) for 28 days, starting from the first day of complementary feeding at around 4–6 months of age. Infants will be presented with a brassica (broccoli), followed by a green leafy vegetable (spinach) and sweet fruit (pear) at 9 months of age. The primary outcome measures of intake of each food will be assessed using a weighed food diary. Secondary outcome measures of overall intake, liking and wanting of vegetables will be assessed using a food frequency questionnaire, liking tool and video coding tool, respectively, at 9, 12, and 24 months of age. Infant growth and iron status will be assessed as part of health screening and monitoring at baseline, post intervention and 9 months of age. Other biological samples to be collected include infant stool samples, vitamin D (mother and infant), iron status (mother), and mothers’ diet.

**Discussion:**

This randomised, controlled trial will be the first to our knowledge to investigate a “vegetables first” approach to complementary feeding on infants’ liking and intake of vegetables in New Zealand. Comparison against standard practice (fruit and vegetables as first foods) should complement other trials underway, such as the Baby’s First Bites and Nordic OTIS trial. Results may contribute to the evidence supporting complementary feeding guidelines in New Zealand and worldwide.

**Trial registration:**

Australian New Zealand Clinical Trial Registry ACTRN12619000737134. Registered on 16 May 2019.

**Supplementary Information:**

The online version contains supplementary material available at 10.1186/s13063-021-05374-7.

## Background

Children are encouraged to eat plenty of different vegetables daily in order to meet a range of nutrient requirements for growth and development, immune function, and digestive health [1, 2]. Children with adequate vegetable intake may have a lower risk of obesity [3] and cardiovascular disease in adulthood [4, 5], and be more likely to develop healthy eating habits for life [6, 7]. Yet children’s vegetable consumption remains low worldwide [8–12]. In the UK, only 14% of children (5–7 years) eat the recommended five or more portions of vegetables and fruit per day [12]. Vegetable intake in the US is similarly low, with the FITS study finding 30% of children 12 months or older not consuming any vegetable servings on a given day [13]. New Zealand children (2–4 years) are doing better but intakes are still inadequate, with 46.1% and 71.2% of children consuming enough vegetables and fruit, respectively [10].

Reasons for poor vegetable consumption may relate to many factors, including a dislike of bitter taste and poor access [13–15]. Infants have an innate preference for sweetness since breastmilk is sweet and may find bitter taste, such as in dark leafy greens, particularly difficult to accept [16–18]. Meanwhile, children from food insecure households may have an additional challenge of accessing a variety of vegetables [19]. Eurostat data found 5.5% of UK households with children were unable to afford meat, fish, or a vegetarian alternative every second day [20]. In the US, an estimated 14% of US families with children experienced food insecurity in 2018 [21]. Similarly, although most New Zealand children live in food-secure households, a substantial number do not (19%) [22] and so are less likely to have vegetables purchased and offered to them [23].

It is known that offering infants a variety of vegetables from the start of complementary feeding may promote liking through familiarisation and facilitate intake throughout childhood [24–26]. However, many infants receive fruit and sweet tasting vegetables (e.g. pumpkin, sweet potato) as their first foods [27, 28]. Furthermore, most commercial infant foods are largely fruit or sweet/starchy vegetable based [29–31]. In a sample of traditionally spoon fed New Zealand infants (n = 628), 1% received “only fruits, no vegetables”, 17% “mainly fruits, some vegetables”, 46% “half fruit, half vegetables”, and 4% “only vegetables, no fruits” when solids were first introduced; just over half were consuming iron-rich foods (meat or infant cereal) at 6 months of age [32]. A recent systematic review of practices to promote vegetable acceptance in the first three years of life concluded that introducing vegetables at the beginning of complementary feeding, giving a different type of vegetable every day and ensuring repeated exposure to the same vegetable following an interval of a few days are the most promising strategies to promote vegetable intake in early childhood [25].

The prioritisation of vegetables only from the start of complementary feeding is known as a “vegetables first” approach to complementary feeding. Only a handful of studies investigating the effects of this approach have been published, with none in New Zealand [33–37]. Barends et al. compared the effects of repeated exposure and starting complementary feeding with vegetables only across four different treatment groups over 18 days. They found that starting complementary feeding with vegetables, but not with fruits, may promote vegetable acceptance and that liking correlated positively with intake. Their follow-up study [35] suggested that starting complementary feeding with vegetables only results in higher daily vegetable consumption until at least 12 months of age; however, further investigation was needed on how to maintain this effect until 24 months of age. Three other studies suggest vegetables as first foods may improve vegetable acceptance later, at least in the short term [33, 36–39]. However, comparability of findings remains limited due to considerable variability in study designs, small sample sizes, and/or poor ecological validity (e.g. conducting trials in the laboratory rather than the home environment). Standardisation across studies could be improved with the use of recent development and validation of tools to assess vegetable liking, such as the Feeding Infants: Behaviour and Facial Expression Coding System (FIBFECS) [40] or an in-home adapted elaborate method for liking tool [41].

Historically, most guidelines on complementary feeding have included vegetables as first complementary foods but alongside fruit and iron-rich foods without a prescribed sequence [1]. The systematic evidence compiled by the UK Public Health England and Scientific Advisory Committee on Nutrition (SACN) [42] however has informed the current NHS recommendations to give a single vegetable and fruit as first foods [43]. While there may be enough evidence to start recommending vegetables as first complementary foods, there is still a need for more longitudinal randomised controlled trials (RCTs) [24, 38, 44, 45]; especially those comparing infants receiving vegetables only to standard practice. Two other trials examining the effects of providing vegetables as first foods on vegetable acceptance are in progress, including the Baby’s First Bites (BFB) trial in the Netherlands and the OTIS Nordic trial. In the BFB, infants are randomised to receiving, with or without a positive feeding programme, either fruits and a sweet vegetable or a variety of vegetables. However, all infants start complementary feeding with rice-flour porridge and then vegetables as their first tastes [45]. The Nordic OTIS trial is comparing effects of the recommended, Swedish complementary diet (i.e. starting with baby cereals, commercially available baby foods) to one based on Nordic foods (i.e. increased plant foods including fruit and vegetables and reduced sweets, dairy and meat) on food acceptance [44]. Infants in the Nordic group are systematically introduced to fruits (e.g. apples, raspberry, buckthorn/lingonberry, cranberry) and vegetables (green peas, cauliflower, turnip, daikon) from the start of the intervention, rather than vegetables only.

RCTs are one of the most rigorous ways to establish cause-effect relationships between treatment and outcomes [46], and RCT data is a gold standard for translating evidence into practice [47]. Our RCT will test the hypothesis that exposure to vegetables only during the first 4 weeks of complementary feeding increases later intake and liking of vegetables in infants, compared to a control group of fruit and vegetables. If this is supported, our results could contribute to the evidence for recommendations for a “vegetables first” approach to complementary feeding in New Zealand and beyond.

### Hypothesis

Exposure to vegetables only during the first 4 weeks of complementary feeding increases later intake and liking of vegetables in infants, compared to a control group which includes both fruit and vegetables.

### Aim

The overall aim of this study is to determine whether exposure to vegetables only during the first 4 weeks of complementary feeding increases later intake and liking of vegetables in infants, compared to a control group which includes both fruit and vegetables.

## Methods/design

This study is designed as a randomised controlled trial comparing two parallel groups following either a “vegetables first” approach to complementary feeding or standard practice of feeding fruit and vegetables. This involves a 4-week intervention period starting from the beginning of complementary feeding (between 4 and 6 months old), with the primary endpoint of vegetable intake at 9 months of age (Fig. 1). The duration of the intervention targets the sensitive period for taste development [48], is logistically feasible, and allows for a timely progression to other foods and textures (e.g. mashed) that is expected by around 7 months. An endpoint of 9 months old aims to capture effects over time without significant loss to follow-up, and enables the study foods to be retested in an age-appropriate form before infants have transitioned to family foods at 12 months of age.

**Fig. 1 Fig1:**
[figure not shown]
Schematic diagram of study design. ^1^Questionnaires: eligibility, demographics, baby eating behaviours, and pregnancy/lactation dietary questionnaires. ^2^Blood biomarkers: serum ferritin, C-reactive protein (CRP), and haemoglobin. ^3^Weight, head circumference, and length. ^4^Includes delivering all study materials, protocol instructions, and information on complementary feeding. ^5^Blood samples to assess the status of mother’s iron/vitamin D and infant’s vitamin D. ^6^Infant stool sample collected by mother 1 week or less before infant receives the first intervention food/test meal. Lab, laboratory (Massey University Human Nutrition Research Unit); D, day; w, week; m, month; t, time-point; FFQ, food frequency questionnaire; Q, questionnaire

### Participants

Mother-infant pairs (4 to 6 months old) living in Auckland will be invited to register on the study website (www.vegesfirststudy.co.nz) [49] advertised on social media, email, and community notice boards. Based on the findings of Barends and colleagues [35], we calculated that 65 participants (a minimum of 52 participants, and allowing for a 20% potential dropout rate) would be required for each arm of the trial to demonstrate a clinically significant difference at 80% power and 5% statistical significance. Power calculations used a 21-unit difference of vegetable intake (grammes) between intervention group and control, and a mean standard deviation of 43 and 29 units, respectively. The sample size was calculated using the formula below [50]:
$$ \mathrm{N}={2\upalpha}^2\mathrm{K}/{\left({\upmu}_2-{\upmu}_1\right)}^2 $$where N is the sample size required per group, SD is the pooled standard deviation, α is the SD, K is the constant (7.9 denotes 80% power and 5% significance), and (μ_2_ – μ_1_) is the difference in vegetable intake (grammes) between groups.

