### Statistical analysis

Statistical analysis will be performed using IBM SPSS version 25.0 (IBM Corp. Released 2017, IBM SPSS Statistics for Windows Version 25.0. Armonk, NY, IBM Corp.). Data will be cleaned and checked for coding errors and completeness. To assess if data is normally distributed, the Kolmogorov-Smirnov and Shapiro-Wilk tests and normality plots will be used. Data that is not normally distributed will be transformed using log transformations to improve normality. Mean (standard deviation) and median (25, 27 percentiles) will be used to report normal and non-normal data, respectively. Transformed data will be reported at geometric mean (95% CI) following back transformation, and categorical data as frequencies.

Baseline characteristics of infants and mothers will be compared across intervention groups using the independent *t*-test or Mann-Whitney test for continuous variables (e.g. infants’ age, weight, breastfeeding duration, and mothers’ age), and chi-square tests for categorical variables (e.g. gender, milk feeding type, and mothers’ education).

For the primary analysis at 9 months, Independent t-test or Mann-Whitney test will be used to assess differences in vegetable intake and other food acceptance variables, depending on data distribution.

Additional analyses will be performed to investigate if the intake of intervention foods and mothers-rated liking and rate of acceptance after 4 weeks are correlated (using Pearson’s or Spearman’s correlations depending on data distribution).

Given the nature of the intervention, per protocol (PP) analyses will be conducted. Although this may compromise the integrity of randomisation and reduce sample size, PP should help address dilution effects of non-compliance/missing data that is associated with intention-to-treat analysis. PP may also provide more information on the efficacy of the treatment. Reasons for excluding patients (e.g. loss to follow-up, major deviations from the protocol) will be fully reported. All statistical tests will be two-tailed with an alpha value of P < 0.05, and corrections applied for multiple comparisons where indicated.

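### The planned sample size is stated two ways, 120 pairs and 65 per arm (130), and the minimum of 52 per arm cannot be reproduced from the printed formula and inputs; the effect on power is small

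*Protocol article*

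**What the plan says.** Two places in the protocol article fix the size of the trial.

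- Abstract, Methods/design: "One-hundred and twenty mother-infant pairs living in Auckland, New Zealand, will be randomised".
- Participants: "we calculated that 65 participants (a minimum of 52 participants, and allowing for a 20% potential dropout rate) would be required for each arm".

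The Randomisation, blinding, and concealed allocation section sets allocation at 1:1.

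The Participants section also gives its inputs. The effect is stated as "Power calculations used a 21-unit difference of vegetable intake (grammes) between intervention group and control", with "a mean standard deviation of 43 and 29 units, respectively". The target is set "at 80% power and 5% statistical significance". The formula is N = 2 × SD² × K / (difference in means)² per group, where "K is the constant (7.9 denotes 80% power and 5% significance". The legend says that the SD is pooled, but assigns the symbol alpha to it. The Statistical analysis section adds: "All statistical tests will be two-tailed with an alpha value of P < 0.05".

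**The concern.** There are two separate problems.

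First, the planned total is 120 in one place and, by implication, 130 in another. The gap is not a dropout adjustment, because 65 per arm already includes dropout. A trial that stops at 120 is fully recruited by the Abstract and ten pairs short by the Participants section.

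Second, the article prints a formula and every input it needs, yet the result it reports is not the one that these inputs give. A reader cannot tell which pooled SD was used, or whether a further inflation was applied. The claim of 80% power then rests on a number that cannot be checked.

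**Working it through.** **Inputs.** Difference 21 g, SDs 43 and 29, K = 7.9, dropout 20%, minimum 52 and target 65 per arm (Participants); 1:1 allocation (Randomisation section); two-tailed 5% (Statistical analysis); 120 pairs (Abstract). K fits a two-sided 5% test at 80% power: the sum of 1.960 and 0.842, squared, is 7.85.

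**The plan's dropout step.** 52 ÷ (1 − 0.20) = 65. This reproduces exactly.

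**Totals.**
- 2 × 65 = 130, against 120 in the Abstract: 10 pairs, or 10 ÷ 130 = 7.7%, fewer.
- 120 ÷ 2 = 60 per arm; 60 × 0.80 = 48 evaluable, against the minimum of 52.
- To keep 52 of 60, dropout could be at most 8 ÷ 60 = 13.3%.

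**The printed formula.**
- Equal-weight pooled SD: the mean of 43² = 1849 and 29² = 841 is 1345, so SD = 36.7. N = 2 × 1345 × 7.9 ÷ 441 = 48.2, or 49 per arm. After dropout, 49 ÷ 0.8 = 61.25, so 62 per arm and 124 in total.
- Simple mean SD of 36: N = 2 × 1296 × 7.9 ÷ 441 = 46.4, or 47 per arm. After dropout, 47 ÷ 0.8 = 58.75, so 59 per arm and 118 in total.
- A noncentral-t calculation gives 49 and 48 per arm for the two SDs, so the choice of method does not explain 52.

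**What would give 52.**
- Solving for the SD: √(52 × 441 ÷ (2 × 7.9)) = 38.1. An SD just above 37.7 is enough if a result just over 51 is rounded up.
- Input rounding: with a difference of 20.5 and SDs of 43.5 and 29.5, N = 2 × 1381.25 × 7.9 ÷ 420.25 = 51.9. At the opposite edge (difference 21.5, SDs 42.5 and 28.5), N = 44.75. So 52 is just inside the range that rounding allows.
- Size-weighted pooling: the pooled variance is 841 plus 1008 × w, where w is the share of the source sample in the SD-43 group. Taking w of about 0.58 to 0.61 gives an SD of about 37.7 to 38.1, and so 52. This is an assumption; the article does not give the source group sizes.
- Mann-Whitney inflation: 49 ÷ 0.955 = 51.3, so 52. The test is named in the Statistical analysis section, but the Participants section credits only the formula.
- One-sided 5% with an SD of 43 alone also gives 52, but contradicts K, the pooled SD and the two-tailed testing.

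**Power for 21 g with SDs 43 and 29, two-sided 5%.**

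| Evaluable per arm | Normal approximation | Welch t |
|---|---|---|
| 48 | 80.1% | 79.2% |
| 52 | 83.1% | 82.3% |

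As a check on the first cell: 21 ÷ (36.67 × √(2 ÷ 48)) − 1.960 = 0.845, which corresponds to 80.1%.

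With the unrounded constant, the equal-weight formula gives 2 × 1345 × 7.85 ÷ 441 = 47.9, so 48 per arm; 48 ÷ 0.8 = 60, or 120 in total. The Abstract's figure is therefore compatible with the printed inputs, though the article does not say that it was derived this way.

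**The case against.** The strongest reply is that 52 has not been shown to be wrong. The printed inputs are whole numbers, a pooled SD is ordinarily weighted by group size, and either route can reach 52. The step from 52 to 65 is exact, and any excess over 49 is conservative. This stands. The fair statement is that 52 cannot be reproduced from what is printed, not that it is an arithmetic error.

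A second reply is that nothing material is lost, because 48 per arm still gives essentially 80% by the plan's own normal-approximation method. This also stands, and it limits the severity. It does not remove the conflict between 120 and 130, which does not depend on how the SDs are pooled.

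Stronger readings are tempting, but the article does not support them.

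- **Inputs are daily quantities.** The Background says that the follow-up study used for the inputs "results in higher daily vegetable consumption until at least 12 months of age", so a reader might infer that 21 g and the SDs are daily amounts and that the power does not apply to single test foods. That sentence summarises a finding; it does not say where the power inputs came from, and the source is not at hand.
- **An SD of 43 g is impossible for one test meal.** This needs a one-sachet ceiling on the 9-month meal. No portion size is given for that meal. The sachet weights in the Infant foods section describe the four-week intervention foods, and broccoli, the first test food, is not in Table 1.
- **Per-protocol exclusions come on top of the 20%.** The Statistical analysis section counts loss to follow-up among the reasons for exclusion, so the two may overlap.

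**Conclusion.** The sample size is wrong as written, at minor to moderate severity. The article requires 65 per arm (130 pairs, 52 evaluable per arm) and also plans to randomise 120, which leaves 48 per arm at 20% dropout. That conflict needs only the stated 1:1 allocation and dropout rate.

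The minimum of 52 is not reproducible: the printed inputs give 47 to 49, depending on how the SDs are combined. It may still be traceable to inputs or pooling that the text does not show.

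It would be an overstatement to call the trial underpowered. On the printed difference and SDs, 120 pairs with 20% dropout give about 79% (Welch) to 80% (normal approximation), roughly three percentage points below what 52 per arm would give. There is no slack if losses exceed 20%.

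**What to change.** Keep 120 as the single target and restate the Participants section to match: 60 per arm randomised, 48 evaluable after 20% dropout, and about 79% to 80% power for a 21 g difference with SDs 43 and 29 at two-sided 5%.

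Replace 52 and 65. If they are kept, state the pooled SD that was used and how it was obtained, and acknowledge that 120 falls short of the resulting 130.

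In the formula legend, use a symbol other than alpha for the SD, since alpha normally denotes the significance level.

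This is a change of text only and adds no participants. The cost is that the stated power may become marginally less favourable. Raising the target to 130 instead would not be free, because it means ten more pairs, and the power figures do not require it.

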### Inclusion and exclusion criteria

Infants will be eligible for this study if they are born term (37 weeks or greater), of normal growth/weight, and have no known food allergies, chronic diseases, or medical conditions. Infants must not have started complementary feeding and must live in Auckland. Mother’s proficiency in English is needed given the requirement to complete assessment tools as part of the secondary outcomes. Participants will be excluded if they demonstrate repeated non-adherence to key study procedures or are not able to complete the 4-week intervention period.

### Setting

The study, data collection and analyses will take place in Auckland, New Zealand, from May 2019 to October 2021. Auckland is the major commercial city of New Zealand, with an ethnically diverse population of 1.6 million and around 21 thousand child births recorded in 2018 [51].

### Infant foods

Freeze-dried infant foods are specifically developed for the study by the researchers. According to study specifications, these are manufactured by FreshAs° who specialise in the production of high-quality freeze-dried vegetables and fruits and are based in Auckland, New Zealand. Vegetables and fruits are selected based on availability, infant nutrition guidelines, total sugar content per 100 g, and colour. A Dietitian and Speech and Language Therapist who specialises in child feeding and development will conduct recipe testing in the laboratory. This confirms that to reconstitute the powders into age-appropriate infant purées, each sachet requires the addition of 50 ml of water (except potato and green bean which require 80 ml). The food is then heated in the microwave for three 20-s intervals, stirred in between, and then cooled for 10 min until it is at a safe temperature for infants to consume. Final instructions are provided on recipe cards to participants.

The foods provided to the intervention group will be less sweet than controls (< 4 g total sugar per 100 g) and made from vegetables only (Table 1). The control group receives foods that will be sweeter than intervention (> 4 g total sugar per 100 g) and fruit based, resembling commercial infant foods that are currently available on the market. Following nutrition guidelines, the study will provide a range of different coloured vegetables, including green, purple, white, and orange. However, it will not be possible to provide an orange-coloured food for the intervention group due to limitations to the freeze-drying method and high sweetness profile of available orange-coloured vegetables. Therefore, the intervention group will be offered a second green food, named “Kākāriki”, which is the Māori translation for green and so should resonate with New Zealand families.

**Table 1 Tab1:** Infant foods allocated to the intervention and control group

Food name	Food ingredient (%)^a^	
	Intervention group	Control group
Green purée	Spinach (80%), potato (20%)	Apple (90%), spinach (10%)
White purée	Potato (100%)	Pear (100%)
Purple purée	Beetroot (70%), potato (30%)	Pear (98%), beetroot (2%)
Orange purée	Not applicable	Pumpkin (100%)
Kākāriki purée	Green bean (100%)	Not applicable

^a^Total dry weight is 8 g per sachet; wet weight is 80 g.

At baseline, mothers will receive enough food to provide up to three meals per day for the duration of the intervention and will be able to access additional sachets from the Massey University Human Nutrition Research Unit (HNRU) as required. To ensure infants meet iron intake requirements while participating in the study, mothers with an infant starting complementary feeding at 6 months of age will be especially encouraged to provide their own meat (beef, fish, or chicken) during the intervention following recipe cards and videos provided.

